## DISCUSSION

In the last two decades, we have achieved a 34% reduction in maternal mortality and a 44% decrease in neonatal deaths. Yet globally, maternal and infant mortality remain unacceptable high, with 223 deaths per 100 000 live births occurring in 2020 and 2.3 million children dying within the first 28 days of life in 2023 [32]. Pregnancy complications and APOs are a major contributing factor in these deaths.

The MOMI Consortium is performing a multi-omics analysis of unprecedented scale across highly diverse populations of LMICs in South Asia and Africa to identify diagnostic markers for early detection of pregnancy complications with the goal to reduce maternal and neonatal mortality and to improve long-term maternal and infant health outcomes. The only other study of similar scale in cohort size, that we are aware of, is currently ongoing in China [4].

A significant milestone of the MOMI project was the harmonisation of study protocols across sites which encompassed study design and sampling methods, adjudication for the key APOs, as well as continued development and optimisation of omics platforms and analysis tools across the partner sites. Adherence to these standardised protocols by all collaborators ensures consistency and quality control in data collection, downstream analysis, and the generation of biologically meaningful insights that are comparable across the sites. Although chronic hypertension could not be systematically excluded at enrolment across all sites, the Consortium applied a conservative, multi-tiered adjudication framework to preserve PE phenotype specificity. Consequently, high-confidence PE cases are unlikely to represent isolated chronic hypertension, and any residual misclassification is expected to bias associations toward the null rather than generate spurious positive findings.

The probing of longitudinal maternal samples with cord blood and placental tissue at delivery by multiple distinct analytical platforms and the subsequent inter-omics data integration will provide a comprehensive view on normal temporal changes of biological pathways in pregnancies progressing to term and birth of a live infant at appropriate weight *vs.* pregnancies resulting in APOs. While each analytical data set may provide insights into one or more APOs, the power of the study lies in the data integration across multiple platforms that will enable a deeper pathway interrogation and increase confidence into signals associated with APOs. Furthermore, the comparative analysis of data across the various sites will reveal site-specific *vs.* common factors that underlie specific APOs. Site-specific variables, such as genetic background, diet, socio-economic factors, or HIV infection are likely to impact pregnancy outcomes of women in their respective cohorts. Nonetheless, we anticipate identifying signatures common to women with the same APO and specific for that APO. The latter signatures will be most valuable for earlier diagnostics and precision interventions that can improve pregnancy care and outcomes globally. Simultaneously, care can be further improved through additional and complementary site-specific interventions. The data obtained from the placenta analysis are expected to provide novel insights into maternal-foetal interactions and, in combination with the data from the infant follow-up visits, inform about the link between placental function and long-term health risks in offspring. Such knowledge will inform implementation of post-partum interventions to ameliorate long-term health consequences for the infant.

The MOMI initiative represents a landmark study and is expected to serve as a roadmap for future investigations relevant to maternal, foetal, and infant health and other disease-related programmes. The principal investigators at each site will share their main findings with scientific communities and local governmental law- and decision-making institutions to pave the way for policy and decision-making processes that can lead to nationwide interventions and influence clinical practices across the country. The combined gain in knowledge and its conversion to actionable diagnostics and therapeutics is expected to have significant impact on the lives of pregnant women beyond LMICs. The inclusion of women from five different countries on two continents, living in rural or urban areas, in the current study is unprecedented and the results will generate insights into pregnancy progression and APOs that is likely to transform the lives of women and infants worldwide, extending its influence beyond the immediate participants.

To summarise, the MOMI study utilises a multi-disciplinary approach towards making informed choices for diagnostic and therapeutic product development. Accordingly, the knowledge gained from this study in terms of identification of reliable and generalisable targetable biomarkers as well as in-depth knowledge on the precise pathogenesis and associated drivers will drive global translational and transformational change in clinical practices on a global scale.

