### Sociodemographic and clinical data

Sociodemographic data (age, partner status, education, tobacco, alcohol and drug use), weight, medical history, parity status and, in case of prior pregnancy, pregnancy history and outcome, were documented at enrolment. A medical exam was conducted at the same time point that included body mass index, blood pressure (BP), and haemoglobin measurement, urine analysis, testing for HIV and other sexually transmitted diseases, assessment of pregnancy symptoms, and a dating ultrasound. Subsequent antenatal visits included determination of GA, recording of pregnancy symptoms since the prior visit, and testing for urine, haemoglobin, BP, heart rate, and weight. At delivery, medical conditions or medications during pregnancy and/or delivery, time of membrane rupture, delivery time, and birth outcome were documented. The foetus’s heart rate and fundal height were also assessed. Data also captured indications for provider-initiated delivery or caesarean section, postpartum complications, neonatal vital status, and Apgar score. Women and infants were seen at least once between six weeks to six months post-delivery. The infant was evaluated for any diseases and medications since birth, and evaluated for infant weight, head circumference, mid-upper arm circumference, temperature, heart and respiratory rates. The mother underwent a pelvic exam and was assessed for weight, BP, heart rate, temperature, and oedema.

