PE harmonisation was the most complex adjudication process (Figure S3 in the **Online Supplementary Document**). Because pre-pregnancy BP measurements and antihypertensive histories were not systematically available across sites, chronic hypertension could not be uniformly excluded at enrolment. To preserve phenotype specificity under these constraints, PE classification relied on a conservative adjudication framework incorporating evidence beyond elevated BP alone, incorporating maternal end organ dysfunction, proteinuria, and foetal growth restriction occurring after 20 weeks’ gestation. Women with BP 140 mmHg systolic or 90 mmHg diastolic at least four hours apart or at two visits and accompanied by proteinuria at the time of assessment were classified as PE. Women with severe BPs (BP 160 mmHg systolic or 110 mmHg diastolic) were classified as PE regardless of proteinuria. Women with proteinuria documented at a visit not coinciding with elevated BP were classified as PE if urinary tract infection was not suspected and end organ dysfunction was present. Maternal end organ dysfunctions considered for PE diagnosis include haematological dysfunction (*e.g.* thrombocytopenia), renal insufficiency, impaired liver function, pulmonary oedema, cerebral/visual symptoms (*e.g.* headaches, scotomata), and ultrasound-based diagnosed foetal growth restriction or birth weight <3 percentile based on GA. In the absence of proteinuria, women with non-severe BP and documented chronic pre-existing hypertension <20 weeks GA were excluded as PE cases. Women without proteinuria were classified as PE if they had severe BP (>160 mm systolic and/or >110 mm diastolic), without consideration of pre-existing hypertension status; had no pre-existing hypertension <20 weeks but presented with indications of end organ dysfunction >20 weeks; or experienced seizure >20 weeks without history of epilepsy (eclampsia). Based on these criteria, four categories of PE cases were defined, ranging from priority 1 (highest confidence) to priority 3 (lowest confidence), with remaining cases classified as non-PE. Once PE cases were confirmed by central adjudication, priority 1 and 2 PE cases were further stratified into early-onset PE and late-onset PE. The former was defined as PE developing before 34 weeks 6 days GA, and the latter as PE developing at or after 35 weeks.

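### The expectation that residual preeclampsia misclassification biases only toward the null does not follow from the adjudication rule: markers of chronic hypertension can be biased away from it

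*Protocol article*

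**What the plan says.** Under Data harmonisation, the article explains that chronic hypertension could not be ruled out uniformly at enrolment, because pre-pregnancy BP and antihypertensive histories were not systematically available. It answers this with adjudication: "PE classification relied on a conservative adjudication framework incorporating evidence beyond elevated BP alone". The rules that follow include these:

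- Women with severe BP "were classified as PE regardless of proteinuria".
- Women without proteinuria are PE if they "had severe BP (>160 mm systolic and/or >110 mm diastolic), without consideration of pre-existing hypertension status".
- The stated exclusion for chronic hypertension is narrow: in the absence of proteinuria, "women with non-severe BP and documented chronic pre-existing hypertension <20 weeks GA were excluded as PE cases".

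Cases are graded from priority 1 (highest confidence) to priority 3. Priority 1 and 2 cases are then split into early and late onset.

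The Discussion draws two conclusions. The first is that "high-confidence PE cases are unlikely to represent isolated chronic hypertension". The second is that "any residual misclassification is expected to bias associations toward the null rather than generate spurious positive findings".

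The enrolment examination described under Sociodemographic and clinical data "included body mass index, blood pressure (BP), and haemoglobin measurement". The covariates named for the association models under Data analysis and data integration are maternal age, body mass index, parity, gestational age at sampling and study site. Neither baseline BP nor pre-existing hypertension is named.

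**The concern.** False-positive cases dilute an association toward the null when they resemble the non-cases on the marker being tested. Women labelled PE who have only chronic hypertension were selected on BP, so they need not resemble non-cases on a marker related to BP. For such a marker, the false cases bring in a difference of their own.

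The study wants signatures that are specific to each adverse outcome and intends to build diagnostics and causal networks on them. If the Discussion's sentence is taken as it stands, a hypertension signal found among PE cases will be read as PE biology, because the article has already said that false positives are not expected from this source. Early-pregnancy samples are the most exposed: chronic hypertension is already present then, whereas PE is defined by events after 20 weeks.

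**Working it through.** **Reproducing the case count.** From Table 2, PE cases by site are 85 + 35 + 7 + 39 + 124 = 290, and 290 / 16,221 = 1.79%, as printed. Non-cases: 16,221 − 290 = 15,931. Early onset 76 + late onset 212 + 2 not derivable = 290. Since only priority 1 and 2 cases were split by onset, the 290 appear to be those two tiers.

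**Inputs the article does not give (assumed).**
- f, the share of labelled PE cases with chronic hypertension only: 5% to 30%.
- c, the same share among non-cases: 0% or 3%.
- d, the marker shift in chronic hypertension: 0.8 SD.

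**Direction of bias.** If the true PE effect on a marker is t, in SD, and c = 0, the expected case–non-case difference is (1 − f) × t + f × d. With t = 0 and general c, it is (f − c) × d.

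| Type of marker (c = 0) | f = 10% | f = 20% | f = 30% | Direction |
|---|---|---|---|---|
| PE only: t = 0.40, d = 0 | 0.36 | 0.32 | 0.28 | toward the null |
| Chronic hypertension only: t = 0, d = 0.80 | 0.08 | 0.16 | 0.24 | spurious |
| Weak for PE, strong for hypertension: t = 0.20, d = 0.80 | 0.26 | 0.32 | 0.38 | away from the null |

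Only the first row behaves as the Discussion says.

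**Size against sampling error.** Treating the contrast as an unadjusted, unweighted comparison of two means, SE = √(1/290 + 1/15,931) = 0.0593 SD. For t = 0 and d = 0.8:

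| f | Shift, c = 0 | z | Shift, c = 3% | z |
|---|---|---|---|---|
| 5% | 0.040 | 0.7 | 0.016 | 0.3 |
| 10% | 0.080 | 1.4 | 0.056 | 0.9 |
| 20% | 0.160 | 2.7 | 0.136 | 2.3 |
| 30% | 0.240 | 4.1 | 0.216 | 3.6 |

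The full-cohort contrast is relevant because proteomics and metabolomics are planned for all longitudinal maternal specimens. Smaller comparators change little. At f = 20% and c = 0, z is 0.16 / 0.0604 = 2.6 against 5000 random sub-cohort members, and 0.16 / 0.0678 = 2.4 against 870 controls (1:3). The corresponding chances of p < 0.05 are about 76% and 66%.

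**Does replication across sites remove it?** The same 0.16 SD shift gives site-level z values, from Table 2 counts, of 1.8 (Tanzania), 1.5 (Zambia), 1.0 (Pakistan), 0.9 (GAPPS Bangladesh) and 0.4 (AMANHI Bangladesh). None reaches 1.96 alone. A genuine PE marker of the same size would give the same values, so replication filters on size and consistency and cannot tell the two apart. A bias that one harmonised rule produces at every site can replicate.

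**The case against.** Several points on the other side stand.

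- The article says the bias is expected to go toward the null. It does not say that it can go no other way, and for markers unrelated to chronic hypertension it is right.
- The lowest-confidence tier appears to be outside the 290 already. The tier given to women who qualify on severe BP alone is in Figure S3, which is not shown. If it is priority 3, an analysis of priority 1 and 2 cases loses this route. The article does not settle this, and its sentence covers any residual misclassification.
- Maternal age and body mass index are prespecified covariates, so part of the difference between women with and without chronic hypertension is adjusted for. Baseline BP is not among the named covariates.
- False discovery rate control would stop many isolated signals of this size. At z = 2.7 (p about 0.007), with 11,000 metabolite features and an assumed 5% level, a Benjamini–Hochberg declaration needs about 0.007 × 11,000 / 0.05, or roughly 1500, features at least as extreme. At f = 30% (z = 4.05) it needs about 12. This limits chance findings, but it does not turn a biased contrast into an unbiased one. Prediction models that pool many weak features do not pass through that filter.
- Replication across sites, with validation in GARBH-INi, is a real check against artefacts of a single site.

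A reader might go further and infer that PE signatures from this study will be false, or that the stated safeguards are worthless. The article does not support that: f, c and d are unknown, and at f = 5% the effect is lost in noise. A reader might also see a second contradiction in the severe-BP threshold, printed once without a comparison sign and once with a greater-than sign. The non-severe threshold also lacks its sign, so a character lost in text extraction is the likelier explanation, and no weight is put on it.

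**Conclusion.** The direction-of-bias statement is unsupported as written. It holds for one class of marker and fails for markers of chronic hypertension, which the adjudication rule leaves room for. The rule also conflicts with the article's own description of a framework that looks beyond raised BP, since severe BP alone is sufficient for classification as PE.

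The size cannot be established from the article. With d = 0.8 and c = 0, the false shift runs from 0.04 SD at f = 5% (z about 0.7) to 0.24 SD at f = 30% (z about 4.1), with 0.16 SD (z about 2.7) at f = 20%. Allowing c = 3% lowers the 20% figure to 0.136 SD (z about 2.3). These values rest on an unadjusted two-group comparison and on the assumption that the 290 include women with chronic hypertension only. What is at risk is the label PE-specific, not the whole PE analysis.

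**What to change.** 1. Delete the toward-the-null sentence, or limit it to markers unrelated to chronic hypertension.
2. Keep the adjudicated PE definition as the main analysis. Making exclusion of every woman with early raised BP the main analysis would replace the consortium's case definition, and would also drop women whom adjudication counts as PE on other evidence.
3. Report PE cases by entry criterion and priority tier, and by hypertension status before 20 weeks (present, absent, unknown), using the enrolment BP. Zambian women enrolled at 20 weeks or later would be unknown unless an earlier record exists.
4. Add two sensitivity analyses: one that excludes cases qualifying on BP alone or with early raised BP, and one that adjusts for enrolment BP.
5. Call a signature PE-specific only if it persists in both. Judge persistence by the direction and size of the estimate, since p-values will weaken as cases are removed.
6. The authors should reconcile the description of evidence beyond BP with the severe-BP rule. Which of the two should give way is a clinical matter for them.

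The cost is some wording and a modest amount of extra analysis on data already held. Intervals in the exclusion analysis will be wider, by an amount that depends on how many cases leave. Adjustment for enrolment BP may also weaken a genuine marker that is correlated with early BP. Early BP will not identify treated women, because antihypertensive histories were not systematically available, so some residual misclassification should still be acknowledged.

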## Additional material

Online Supplementary Document
